## Abstract

**Background:**

The majority of breast cancer patients suffer from persistent impairments after completion of their primary oncological therapy. Cancer-related fatigue (CRF) in particular is a multidimensional syndrome having a profound negative impact on the quality of life. To counter CRF symptoms, physical activities are suggested as first-line interventions, mind-body therapies have been shown to be effective, and music therapy can also reduce anxiety and stress in breast cancer patients. Tango therapy that combines various elements can have an impact on physical, psychological, and cognitive abilities and could therefore have a beneficial effect on breast cancer patients. The purpose of this study is to investigate whether a 6-week tango module is suited as a therapeutic approach for people after primary breast cancer therapy to favorably influence their quality of life, especially CRF levels.

**Methods:**

Sixty patients with a diagnosis for stage I–III breast cancer 12–48 months before enrollment and with CRF (age > 18) will be recruited and randomized 1:1 to a tango or a waiting-list group. Movement concepts using elements of Argentine tango (self-awareness, musical and spatial perception, self-perception, playfulness, shared experience) will be examined with the participants during six consecutive weekly 1-h tango sessions. The primary outcome will be the improvement of CRF (German version of the Cancer Fatigue Scale), and the secondary outcomes will be the improvement in sleep quality (Pittsburgh Sleep Quality Index) and quality of life (EORTC-QLQ-C30). Patient-reported outcomes will be measured at baseline and 6 weeks later; follow-up will be performed 6, 12, and 24 months after baseline. An evaluation will be performed by means of descriptive data analyses.

**Discussion:**

Argentine tango, as a music-based movement therapy, can influence different skills and may improve several outcomes. The therapeutic use of Argentine tango in the care of breast cancer patients has not yet been reported. It is anticipated that participants receiving the tango module will have improved CRF, sleep, and quality of life scores compared to a waitlist control.

**Trial registration:**

German Clinical Trials Registry (DRKS) DRKS00021601. Retrospectively registered on 21 August 2020

## Administrative information

Note: The numbers in curly brackets in this protocol refer to SPIRIT checklist item numbers. The order of the items has been modified to group similar items (see http://www.equator-network.org/reporting-guidelines/spirit-2727-statement-defining-standard-protocol-items-for-clinical-trials/).

## Introduction

### Background and rationale {6a}

Breast cancer still is the most common cancer in women worldwide [1]. About one-third of breast cancer patients experience moderate to severe fatigue symptoms [2, 3]. Cancer-related fatigue (CRF) is a multidimensional syndrome having a profound negative impact on health-related quality of life (HRQL) and is a very prevalent and distressing side effect among breast cancer patients, which may often persist for many years after oncological treatment [2, 4]. In a systematic review, it was found that an ameliorative benefit on HRQL can be reached with physical activity interventions such as yoga, physical self-management, complementary exercises, art therapies, mind-body exercise therapies, and cognitive-behavioral therapies [5]. Currently, there is convincing evidence that specific doses of aerobic and/or resistance training could improve common cancer-related health outcomes, including fatigue, and it is recommended that physical activities are proposed as a first-line intervention for improving HRQL and counteracting CRF symptoms [6, 7]. Mindfulness-based interventions, such as meditation and yoga, in particular, have been shown to be effective in reducing CRF levels [8]. Unfortunately, a lack of motivation and fatigue and a lack of time are often barriers to physical activity [9]. Several results from systematic reviews reveal mindfulness-based art therapy improves anxiety, depression, fatigue, stress, and HRQL [10–12]. Especially, cancer-related cognitive complaints such as fatigue, insomnia, and psychological distress might be managed through multimodal approaches. Another form of exercise therapy, which includes cognitive, emotional, and volitional elements, is eurythmy therapy [13], and interestingly, a multicenter study of 126 breast cancer patients reported that a multimodal approach that included eurythmy therapy and psychoeducation resulted in an improvement in HRQL and a significant reduction in symptoms of fatigue [14, 15]. Also, behavioral techniques appear to play an important role in influencing psychosocial functioning and cognitive impairments [16]. Data of a systematic review found a positive role of life review on spiritual well-being, overall distress, and HRQL in patients with terminal or advanced cancer [17], which is important not only at the end of life. For instance, we reported that in breast cancer patients, elaborate consultations and life reviews conducted at first diagnosis were associated with a significant reduction in fatigue symptoms and relevant improvements in HRQL [18, 19]. Music therapy is another suitable creative arts treatment for improving psychological and physical outcomes in cancer patients, and a beneficial effect on anxiety and especially a moderate effect on fatigue and HRQL were found [20]. Hence, dance as a combination of physical activity, music, and mindful elements might be an appropriate and effective approach, to address CRF and to improve HRQL [21]. Protocols for randomized controlled trials of dance therapies for breast cancer patients have been published, to investigate different and various aspects. For example, it has been investigated whether dance therapy can relieve symptoms and stress in breast cancer patients, during radiation therapy [22], and whether traditional Greek dance [23] or belly dance [24] shows physical or psychological benefits. Furthermore, a pilot trial of 31 female cancer survivors and their partners examined ballroom dance, to improve their HRQL [25]. With a dance program for patients with breast cancer across five European countries, positive changes on HRQL and improvements of emotional and social scales were observed [26], and in a feasibility study, the efficacy of a balance training program using elements of Argentine tango for cancer survivors was assessed [27]. Argentine tango is a music-based movement therapy which can influence physical, psychological, and cognitive skills. In addition, it meets women’s desire for social interaction [28]. Tango as a dance form has the advantage that it can be danced improvisationally in a variety of ways: without former experience, in changing roles, paired or in groups, as well as with or without physical contact. Interestingly, a systematic review revealed that Argentine tango has a tendency for positive effects on fatigue and HRQL in Parkinson’s disease patients [29]. To date, no results of high-quality randomized controlled trials have been published on the effectiveness of dance therapies for cancer survivors. The aim of this study is to investigate whether therapeutic tango can improve self-reported quality of life, particularly fatigue levels, in breast cancer survivors.

### Objectives {7}

This study protocol describes a randomized controlled trial for patients with breast cancer and increased CRF receiving either Argentine tango in a tango group or no Argentine tango in a waiting-list control group. The primary outcome measure is the change of CRF levels after 6 weeks. (A) The CRF changes of patients of the tango group will be compared to the waiting-list control group, and (B) prior to and post the 6-week Argentine tango treatment, the CRF changes are evaluated for the whole study cohort. The primary hypothesis is that a module consisting of six consecutive weekly 1-h Argentine tango lessons will promote a significant reduction of fatigue symptoms. Secondary objectives are the improvement of self-reported sleep quality and HRQL, prior to and post the Argentine tango treatment, and to explore the effects after 6, 12, and 24 months follow-up.

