### Interventions

#### Explanation for the choice of comparators {6b}

The comparator is a waiting-list control group. All participants will be randomized to either the tango group or the waiting group. The participants of the waiting group will continue routine activities during the 6-week waiting period. During follow-up, patients from the waiting-list control group will receive the same Argentine tango module as the participants of the tango group. The follow-up assessments for both trial arms will be the same (Fig. 1).

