## Statistical methods

### Statistical methods for primary and secondary outcomes {20a}

All statistical analyses will be performed using Excel 2010 (Microsoft, USA) and the software R (R version 4.0.5) [38]. Baseline data will be summarized using descriptive statistics. Continuous variables will be described as means with standard deviation and median with interquartile range (IQR), categorical variables will be summarized as frequencies and percentages. Student’s *t*-tests will be applied, and *p*-values < 0.05 are considered to be significant. For the characterization of group differences, Pearson’s chi-squared tests with Yates’ continuity correction and Student’s *t*-tests will be performed. The detection of longitudinal effects will be characterized with Student’s *t*-tests and to identify influencing factors and to address potential sources of bias and potential confounders, and adjusted multivariable linear regression analyses will be performed. In order to yield reliable model results, stepwise regression selections will be performed, and models with high adjusted *R*^2^ will be chosen. According to Cohen’s interpretation [39], *R*^2^ values between 13 and 25% indicate medium, and *R*^2^ values 26% or above indicate high effect sizes. In addition to statistical significance, we will report descriptive statistics and effect size estimates.

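### The primary outcome carries two unranked analyses, one of them an uncontrolled before-after change, and the primary hypothesis names no comparator, so the text allows it to be called met without the randomised comparison

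*Protocol article*

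**What the plan says.** Objectives {7} of the protocol article defines one primary outcome: "The primary outcome measure is the change of CRF levels after 6 weeks". Two evaluations follow, joined by a plain conjunction. The first is "A) The CRF changes of patients of the tango group will be compared to the waiting-list control group". The second is "B) prior to and post the 6-week Argentine tango treatment, the CRF changes are evaluated for the whole study cohort". No order, hierarchy or division of alpha is given.

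The hypothesis comes next: "The primary hypothesis is that a module consisting of six consecutive weekly 1-h Argentine tango lessons will promote a significant reduction of fatigue symptoms". It does not say compared with what. The secondary objectives begin only after that sentence, so (B) stands in the primary tier.

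Explanation for the choice of comparators {6b} explains how the whole cohort can enter (B): "patients from the waiting-list control group will receive the same Argentine tango module as the participants of the tango group". Statistical methods {20a} sets a general significance threshold of p < 0.05, plans Student's t-tests for group differences, and adds: "The detection of longitudinal effects will be characterized with" Student's t-tests as well. Sample size {14} assumes d = 0.8, 80% power and two-sided 5% for fatigue, and arrives at 25 per group.

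**The concern.** (A) is protected by randomisation and (B) is not. Participants enter with a CFS-D of at least 12, know when they are receiving tango, and report their own fatigue. Once the waiting list has also been treated, the pooled before-after change has no untreated group beside it. Natural recovery, expectancy and regression to the mean would all be counted as tango effect.

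Because the hypothesis asks only for a significant reduction, a significant (B) with a null (A) fits its wording. The trial could then report its primary hypothesis as met from an analysis that the waiting list was set up to avoid. A lesser problem is that two tests at 5% on one primary outcome raise the overall error rate.

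The two analyses also use different windows. For waiting-list patients the change around tango falls after the waiting period, so (B) does not correspond to a single 6-week point counted from randomisation.

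**Working it through.** **1. The plan's own figure.** For two groups, n = 2(z₀.₉₇₅ + z₀.₈₀)²/d² = 2(1.960 + 0.842)²/0.64 = 24.5, so 25 per group. This reproduces Sample size {14}. With the t distribution it is 26, and 25 gives 79.1% power. The calculation is for a two-group comparison, which is (A). The plan gives no separate calculation for (B). The stated 20% dropout from 60 leaves 60 × 0.8 = 48 pairs for (B).

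**2. Two unranked tests, no tango effect, no time trend.** If independent: 1 − 0.95² = 9.75%. They are not independent, because the tango-arm changes enter both. Simulation with 25 per arm, and a correlation of 0 or −0.3 between a waiting-list patient's two successive changes, gives 8.6–9.1% two-sided. Counting only results in the direction of benefit gives 4.3–4.5%.

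**3. (B) when everyone improves for reasons other than tango.** Paired t-test, n = 48, two-sided 5%. The drift is an assumption; the documents give no figure.

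| Assumed drift (SD of change) | (B) significant |
|---|---|
| 0 | 5% |
| 0.1 | 10% |
| 0.2 | 27% |
| 0.3 | 53% |
| 0.4 | 77% |

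Under the same drifts, with equal drift in both arms, (A) stays at about 5% in simulation (25 per arm).

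**4. Regression to the mean alone.** Only the entry cut of 12 comes from the protocol. Assumed: population SD 10, mean 18 to 30, retest correlation r of 0.6 or 0.7.

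- a = (12 − mean)/10 and λ = φ(a)/(1 − Φ(a)).
- Expected fall = (1 − r) × 10λ.
- SD of change = √[(1 − r)² × 100(1 + aλ − λ²) + 100(1 − r²)].

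Example, mean 18 and r = 0.6: a = −0.6; λ = 0.3332/0.7257 = 0.459; fall = 0.4 × 4.59 = 1.84 points; SD of change = √(0.16 × 51.4 + 64) = 8.5; standardised 0.216, significant in 31% with n = 48.

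That applies the full fall to all 48. Outcomes {12} plans questionnaires around the waiting period as well as around treatment. If the waiting-list patients' pre-tango score is the one taken after waiting, it is not the score they were selected on, so most of their regression is already over. The pooled fall is then about half (0.92 points in the example, or 0.108 SD).

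| Mean | r | Fall (points) | All 48 affected | Half affected |
|---|---|---|---|---|
| 18 | 0.6 | 1.84 | 31.1% | 11.4% |
| 18 | 0.7 | 1.38 | 24.1% | 9.6% |
| 22 | 0.6 | 1.15 | 14.8% | 7.4% |
| 22 | 0.7 | 0.86 | 12.2% | 6.8% |
| 26 | 0.6 | 0.65 | 8.0% | 5.7% |
| 26 | 0.7 | 0.49 | 7.2% | 5.5% |
| 30 | 0.6 | 0.33 | 5.7% | 5.2% |
| 30 | 0.7 | 0.25 | 5.5% | 5.1% |

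**5. Sample size under the alternatives.** With (A) as the sole primary comparison, alpha stays at 5% and n at 25 per group. Keeping both as primary at 2.5% each would need 2(2.241 + 0.842)²/0.64 = 29.7, so 30 per group (31 by the t distribution). Splitting alpha would still leave (B) without a control.

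**The case against.** The best defence is that (A) is plainly what the authors had in mind. Objectives {7} introduces a randomised trial against a waiting list, lists (A) first, and has it compared whereas (B) is merely evaluated. The Abstract and the Discussion anticipate improvement relative to the waitlist, and the sample size is stated per group. An analysis plan that is not shown may rank the two. The Abstract even speaks of descriptive analyses.

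Much of this stands as evidence of intent. A reader might infer that the plan treats (B) as sufficient, or that the investigators mean to claim efficacy from it. The documents do not say that; they only leave it open. But no section makes (A) the sole test or gives (B) a lower rank, {20a} sets tests and a threshold, and Sample size {14} itself also refers to longitudinal differences. The hypothesis is in this document, so a later ranking would have to override its published wording.

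The defence is also right about size. A reader might infer that regression to the mean makes (B) falsely significant in 10–30% of trials. That needs all 48 participants to be affected and a low population mean; the timing of the questionnaires points to about half being affected, and no mean is given. A sizeable natural recovery is not documented either: participants are 12–48 months from diagnosis, and the Introduction says that fatigue may persist for years. Expectancy could bias (A) too, since the waiting list is not blinded to treatment.

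Finally, a reader might want the same restriction spelled out for the 6-, 12- and 24-month changes. Objectives {7} already makes these secondary and exploratory.

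**Conclusion.** The objective is wrong as written: an uncontrolled before-after change shares the primary tier with the randomised comparison, and the hypothesis can be read as met on it alone. This follows from the wording and does not depend on any assumed figure.

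The size of the bias in (B) cannot be determined from the documents. With 48 pairs and no tango effect, the illustrative range is 5% to 77% significant for an assumed drift of 0 to 0.4 SD of change. Regression to the mean alone gives about 5–11% if waiting-list patients are re-measured before tango, and up to about 31% if they are not and the population mean is as low as 18. Unranked testing by itself puts the two-sided family-wise error at about 9%, with 9.75% as the figure under independence. The planned randomised comparison is sound in principle and is not touched by this point.

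**What to change.** - Name (A), the between-arm difference in CFS-D change at 6 weeks, as the only primary comparison, at two-sided 5%.
- Reword the hypothesis to predict a greater reduction in fatigue than in the waiting-list group.
- Move (B) to the secondary analyses as a descriptive estimate: mean change with 95% confidence interval and no efficacy claim, shown beside the waiting-list change over the 6 untreated weeks.
- Leave the follow-up objectives as they are.

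The cost is wording in Objectives {7} and Statistical methods {20a}, with the amendment notified as {25} provides. No data collection changes, and the stated 25 per group still applies. The article reports that enrolment is ongoing and that no interim analysis is planned, so as of the article the change can be made before any comparative result is known.

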### Data collection and management

#### Plans for assessment and collection of outcomes {18a}

The primary outcome is change in CRF measured with the validated CFS-D questionnaire [30]. The secondary outcomes are sleep quality, measured with the Pittsburgh Sleep Quality Index (PSQI) [31], and patient’s HRQL, measured with the European Organization for Research and Treatment of Cancer Questionnaire C30 (EORTC-QLQ-C30) [32].

After obtaining written informed consent and inclusion in this study, sociodemographic and clinical data are surveyed, and questionnaires will be given to participants. All questionnaires will be collected prior to and post-treatment and during follow-up 6, 12, and 24 months after the start of the tango module (Fig. 1).

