CRF is a multidimensional syndrome, frequently occurring with other neuropsychological symptoms also acting at sleep/wake centers in the brain [46]. Furthermore, it has been observed that CRF frequently occurs alongside and is interrelated with sleep disturbances [47]. Interventions that affect the biorhythm may therefore also influence the mood and well-being, as well as might modulate fatigue symptoms of cancer patients. Dance can be understood as a multimodal treatment based on body awareness, expression, and rhythm, combining both psychotherapeutic therapy and physical activity, and can support emotional, cognitive, and spiritual integration [48]. A recent study reported that ballroom dancing may improve functional exercise capacity and may be associated with a high self-efficacy and active lifestyle [49]. However, no effects of this dance training on fatigue symptoms were observed, but there was a limitation to individuals who had a healthy dance partner and presumably exhibited only mild fatigue symptoms, since data were collected only from participants of active dance classes [49]. To address people with breast cancer who suffer from CRF, have low self-confidence, are less fit, and often do not have any appropriate partner for dance exercises, we chose Argentine tango, a dance style that allows adaptation to different conditions and can be performed even under the current pandemic situation by dancing with a surgical mask and in a distance of 2 m. The therapeutic use of Argentine tango to reduce fatigue symptoms in breast cancer patients has not yet been assessed. Argentine tango comprises relaxation techniques, supports balance finding and self- and spatial perception exercises, and thus may influence physical, psychological, and cognitive skills as well as probably also fatigue levels and insomnia. It is expected that receiving the 6-week tango module will significantly reduce fatigue and insomnia symptoms in our breast cancer patients. Previously, we could show that the treatment of breast cancer patients with chemotherapy is associated with a severe increase in fatigue, in particular, of cognitive fatigue [50]. There are hardly any therapeutic options to alleviate such cognitive impairments. It has been reported that Argentine tango can influence and improve cognitive abilities in Parkinson’s patients [29]. Therefore, it is believed that the tango may also have a positive effect on cognitive fatigue in breast cancer patients. The tango group is expected to have a clinically relevant reduction in fatigue and insomnia symptoms compared to the waitlist control. Further benefits related to aspects of HRQL may be observed. In addition, follow-up surveys of the entire cohort will be conducted at 6, 12, and 24 months to examine how this tango treatment will be perceived by the participants and how lasting the effects prove to be.

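### The secondary objectives for sleep quality and HRQL name only a before-after change, although the protocol expects improvement over the waiting list and never makes the randomised comparison their basis

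*Protocol article*

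**What the plan says.** All references are to the protocol article.

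- **Objectives {7}, fatigue.** Two contrasts are set out. Contrast (A) is randomised: "The CRF changes of patients of the tango group will be compared to the waiting-list control group". Contrast (B) is uncontrolled: "prior to and post the 6-week Argentine tango treatment, the CRF changes are evaluated for the whole study cohort".
- **Objectives {7}, sleep quality and HRQL.** "Secondary objectives are the improvement of self-reported sleep quality and HRQL, prior to and post the Argentine tango treatment", followed by an exploration at 6, 12 and 24 months. No comparison arm is named.
- **Abstract, Discussion.** The expectation is that "participants receiving the tango module will have improved CRF, sleep, and quality of life scores compared to a waitlist control".
- **Main Discussion.** "The tango group is expected to have a clinically relevant reduction in fatigue and insomnia symptoms compared to the waitlist control". For HRQL this section is softer and says only that further benefits may be seen.
- **Plans for assessment {18a}.** "The secondary outcomes are sleep quality, measured with the Pittsburgh Sleep Quality Index (PSQI"), together with HRQL measured by the EORTC-QLQ-C30. No contrast is attached to either.
- **Statistical methods {20a}**, a section headed for primary and secondary outcomes. "For the characterization of group differences, Pearson’s chi-squared tests with Yates’ continuity correction" and Student's t-tests are planned. Separately, "The detection of longitudinal effects will be characterized with Student’s" t-tests. One threshold, p < 0.05, applies throughout, and neither use is assigned to a particular outcome.
- **Outcomes {12}.** Every questionnaire is collected around the waiting period as well as around treatment, so control data on both secondary outcomes will exist.

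**The concern.** The Objectives paragraph separates a randomised contrast from a before-after contrast for fatigue. It then words the secondary objectives in the terms of the before-after contrast alone. Other parts of the article expect superiority over the waiting list for the same outcomes, which a before-after change cannot show.

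This differs from the question of how (A) and (B) rank for fatigue. There the randomised contrast is at least stated; for sleep and HRQL it is missing from the objective. Settling the ranking for fatigue would leave this gap open.

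The risk is a secondary conclusion that randomisation does not protect. Participants are selected for raised fatigue (Eligibility criteria {10}), and the Discussion describes fatigue as interrelated with sleep disturbance. Both secondary outcomes are self-reported. Scores may improve through regression to the mean or natural recovery, and a before-after test counts that improvement as tango benefit. The between-arm comparison cancels whatever part of it the two arms share.

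**Working it through.** **1. The plan's own figure.** Sample size {14} assumes d = 0.8, two-sided 5% and 80% power for fatigue, and states 25 per group. By the normal approximation, n per arm = 2 × (1.960 + 0.842)² / 0.8² = 24.5, rounded up to 25. The exact t-test gives 26, with power 79.1% at 25. The stated figure reproduces. It concerns the between-group comparison of fatigue and says nothing about the secondary outcomes.

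**2. Numbers analysed.** 60 randomised 1:1 with the planned 20% dropout leaves 60 × 0.8 = 48, or 24 per arm.

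**3. Assumptions not in the documents.** Tango has no effect. Scores improve for non-specific reasons by δ = 0.2, 0.3 or 0.4 SD of the change score. The protocol gives no SD and no estimate of drift for the PSQI or QLQ-C30.

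**4. Before-after test.** For a two-sided paired t-test at 5%, the chance of significance comes from the non-central t distribution with n − 1 degrees of freedom and non-centrality δ√n. With n = 24 and δ = 0.3, the non-centrality is 0.3 × √24 = 1.47 against a critical value of 2.07, which gives 0.291.

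| Chance of a significant before-after change, no tango effect | δ = 0.2 | δ = 0.3 | δ = 0.4 |
|---|---|---|---|
| One arm, n = 24 | 0.156 | 0.291 | 0.467 |
| Both arms pooled, n = 48, equal drift | 0.274 | 0.530 | 0.775 |
| Pooled, n = 48, drift halved in the waiting arm (mean 0.15 / 0.225 / 0.3) | 0.175 | 0.333 | 0.530 |
| Pooled, n = 48, no drift in the waiting arm (mean 0.1 / 0.15 / 0.2) | 0.104 | 0.175 | 0.274 |

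The last two rows allow for regression that has already happened while the waiting arm waits. They use the average drift over the two arms and ignore the small extra spread caused by the arms differing.

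**5. Between-arm test.** If δ is the same in both arms over the first 6 weeks, it drops out of the difference in change, and the false-positive rate stays at 5%.

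**6. Price of the between-arm test.** For a two-sample t-test at 5% with 25 per arm, power is 79% at d = 0.8, 41% at d = 0.5 and 18% at d = 0.3.

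**The case against.** **The randomised comparison is not missing from the article.** Trial design {8} lists fatigue, sleep quality and HRQL together under the two-arm design. Section {20a} covers secondary outcomes and plans tests of group differences. The Abstract names the waitlist as comparator for sleep and quality of life, and the Discussion does so for insomnia. These places could be read as supplying the comparator that one condensed sentence leaves out. This stands to the extent that a between-arm test is open to the analysts. It does not make that test the basis of the secondary objectives.

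**The before-and-after phrase may describe timing only.** Section {18a} uses similar words for when questionnaires are collected. That reading is possible. Against it, the same paragraph of Objectives uses the phrase for contrast (B), in deliberate distinction from (A).

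**The choice of deciding test can be left to a statistical analysis plan.** That is fair for test-level detail. What is at issue is the objective, which is stated here and does not match the expectations stated elsewhere in the article.

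**The size depends on favourable choices.** Objectives {7} mentions the whole cohort only for fatigue, so pooling the secondary outcomes is not stated. Equal drift in the waiting arm after its 6-week wait is doubtful. Selection is on fatigue rather than sleep, at 12 of 60 points, and patients are 12–48 months from diagnosis. Nothing in the documents supports a particular amount of drift. All of this stands, and the single-arm row is therefore the safer illustration.

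**A stronger reading to avoid.** A reader might infer that the protocol commits to judging sleep and HRQL on uncontrolled change alone, or that it excludes the randomised comparison. Section {20a} and the Abstract do not support that. Power and alpha in Sample size {14} concern fatigue only, and the Abstract describes the evaluation as descriptive, so no confirmatory secondary claim is announced either.

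**Conclusion.** The point holds as an inconsistency in the stated contrast. The secondary objectives carry the wording of the uncontrolled fatigue contrast. The Abstract (sleep and quality of life) and the Discussion (insomnia) expect improvement over the waiting list. Section {20a} permits both kinds of test without giving the randomised one precedence for secondary outcomes.

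Under an assumed non-specific improvement of 0.2, 0.3 or 0.4 SD of the change score and no tango effect, a before-after test would be significant in about 16%, 29% or 47% of trials in one arm of 24. The figures of 27%, 53% and 77% for 48 pooled participants are an upper case that needs equal drift in both arms. The between-arm test stays at 5% when drift is shared. The amount of drift is an assumption throughout; that the before-after test exceeds 5% follows from any non-zero drift.

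The consequence is moderate: the outcomes are secondary, the control data are already planned, and rewording resolves it.

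**What to change.** In Objectives {7}, state the secondary objectives as the tango minus waiting-list difference in change from baseline to 6 weeks, in the PSQI global score and in QLQ-C30 HRQL. In {20a}, say that this between-arm comparison is the basis for conclusions on the secondary outcomes. Report before-after changes, including those after the waiting arm's own module, as supportive and descriptive with confidence intervals.

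The cost is one reworded objective and one matching analysis sentence; no new data or participants are needed. The downside is lower sensitivity. With 25 per arm the between-arm test has about 41% power at d = 0.5, so secondary results may look less favourable than a pooled before-after test would make them.
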